## APPENDIX 7: Hemodynamic assessment report

### Hemodynamic Assessment Report:

Date: \_\_\_/\_\_\_/\_\_\_ Time: \_\_\_

**Clinical/Lab data:** GA: \_\_\_ weeks; B. Wt: \_\_\_ gm

BP: \_\_\_ mmHg; UO: \_\_\_ ml/k/hr; CRT: \_\_\_ secs

pCO2: \_\_\_; SpO2: \_\_\_; FiO2: \_\_\_; rScO2: \_\_\_

NS bolus: ☐ Yes, if Yes, no of times: \_\_\_ ☐ No

Blood products: ☐ Yes, If Yes, specify \_\_\_ ☐ No

Inotropes/Vasopressors: ☐ Yes ☐ No

If yes, drug and the dose: \_\_\_\_\_

Lactate: \_\_\_ mmol/l; Hb: \_\_\_ g/l; C/S: \_\_\_ mmol/l

NIRS: ☐ Normal ☐ Low ☐ High

TNE: ☐ Yes ☐ No

**TNE Findings:** Function \_\_\_\_\_; Cardiac filling \_\_\_\_\_

LVO \_\_\_\_\_; RVO \_\_\_\_\_; SVC \_\_\_\_\_; DA flow \_\_\_\_\_

PV flow \_\_\_\_\_; PDA \_\_\_\_\_; Pul.pres. \_\_\_\_\_

**Hemodynamic state:** ☐ Adequate SBF ☐ Low SBF

☐ Adequate Brain perfusion ☐ Low Brain perfusion

☐ Other, specify \_\_\_\_\_

### Conclusion:

- ☐ Adequate hemodynamic status
- ☐ Compensated CV compromise
- ☐ Decompensated CV compromise

Comments: \_\_\_\_\_

---

## APPENDIX 8: MUSE Trial Study Guideline-Flash Card

Low BP(MBP<3rd Centile) and Normal NIRS( 55 – 85%)

[figure not shown]

Low BP(MBP<3rd Centile) and Low NIRS( <55% )

[figure not shown]

Low BP(MBP<3rd Centile)and High NIRS( >85%)

[figure not shown]

Normal BP(MBP =3-90th Centile) and Low NIRS( <55%)

[figure not shown]

Normal BP(MBP =3-90th Centile) and High NIRS( >85%)

[figure not shown][figure not shown]

High BP(MBP >90th Centile) and Normal NIRS( 55 - 85%)

[figure not shown][figure not shown]

High BP(MBP >90th Centile) and Low NIRS( <55%)

[figure not shown][figure not shown]

High BP(MBP =3-90th Centile) and High NIRS( >85%)

[figure not shown][figure not shown]

Supplement: Supplement 1. — Trial Protocol [file jamanetwopen-e254101-s001.pdf]

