### Study Procedure:

This will be a Non-Blind Randomized Control Trial.

The study will involve the following steps ([APPENDIX 1](#)):

- 1) The study population will be assigned by simple randomization to either Multimodal arm to receive multimodal hemodynamic assessment using the study guideline ([APPENDIX 5](#)) or Standard arm to be treated according to the standard approach operative in RAH NICU.

- 2) ELGANs recruited into Standard arm will have
  - a) Continuous cardiorespiratory monitoring using ECG leads or via an Arterial line, and pulse oximetry and intermittent non-invasive blood pressure monitoring as standard of care in the NICU. Continuous arterial blood pressure monitoring will also be obtained as appropriate when an arterial line has been placed under the clinical team's discretion.
  - b) TNE studies will be performed at the discretion of clinical team for concerns on cardiorespiratory status of the study population.
  - c) The current treatment protocol for hemodynamic compromise at our NICU is starting inotropic support if mean blood pressure (MBP) is less than the gestational age of the infant in the first 72 hours of life.
  - d) Cerebral NIRS monitoring for rScO2 using neonatal sensors is not routinely used in the NICU and its application for the standard arm will be up to clinical team discretion.
- 3) ELGANs recruited to the Multimodal arm will have the same monitoring outlined in 2a in a standardized manner.
  - a) Continuous cerebral NIRS monitoring for rScO2 using neonatal sensor will be attached to the forehead of the infant for first 72 hours of life ([APPENDIX 2](#)).
  - b) Hemodynamic assessment using TNE ([APPENDIX 3](#)) will be performed at 18-24 hours and 66-72 hours of life. Additional TNE studies will be performed at the discretion of the clinical team for concerns on cardiorespiratory status of the study population.
  - c) Zubrow's Normative BP chart will be used and MBP less than the third centile for the gestational age will be taken as low BP for the study.
  - d) Blood pressure values and NIRS data will be integrated along with the clinical/biochemical information every 6 hours as well as whenever there is a deviation from the normal range.
  - e) A comprehensive study guideline comprising of the clinical, biochemical and NIRS data will be used by the study team in such cases to derive to the hemodynamic assessment of the study subject.

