  - f) The findings will be carefully integrated within the clinical context to reach a description of the hemodynamic status of the study infant ([APPENDIX 5 and 7](#)).
- 4) All neonates will have standardized assessment for lead related skin abrasions as per standard practice, neonatal pain and stress assessment (NPASS Score) as part of their standard care.
- 5) Developmental support care will be given by the support person during the TNE assessment as per standard unit practice.

- 6) The discontinuation of either or both NIRS and TNE will depend on the discretion of the clinical team. The reason for the discontinuation will be sorted. This does not constitute a deviation from the study protocol.
- 7) The admission, 24 hours, 48 hours, 72 hours and 7days mean and median VVR and VIS scores will be calculated in both Study and Standard arms. ([APPENDIX 4](#)).
- 8) Urine output will be monitored during the study period as a surrogate for renal function and urine output less than 1 ml/kg/hr will be considered as oliguria.
- 9) SNAPPE-II Scores, which is a validated disease severity score in preterm babies, will be calculated in both study and standard arm at admission, 72 hours and 7 days of life.
- 10) The study team will be available 24/7 for hemodynamic consultation and for the ease of making hemodynamic interpretation, each pathway in the comprehensive guidelines will be transcribed into individual flash cards that will be easily accessible to study team. ([APPENDIX 8](#)).

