## APPENDIX 2: Site for Application of Cerebral NIRS Probe

Cerebral probe will be placed on the midline position for monitoring rScO2 in preterm neonates. Alternative sites could be on the right or left side of the forehead and away from nevi, sinus cavities, the superior sagittal sinus, subdural or epidural hematomas, or other anomalies such as arteriovenous malformations. There are currently no unit specific guidelines for application of neonatal NIRS sensor probe. As such, NIRS probe will be placed similar to a previous trial at our center which is by using Mepitel, one between the skin and NIRS probe interface to reduce any skin irritation that could be caused due to the sensor probe. If during the course of the study period center specific guidelines are developed for placement of neonatal NIRS probe that will be adopted into the study, then. Probe sites would be assessed regularly for lead related skin irritation as part of the standard of care practice in the NICU.

The normal reference range of rScO2 for preterm infants varies between 55% and 85% and this would be used for the proposed study. Using NIRS derived cRSO2, Cerebral Fractional Oxygen Extraction (CFOE) will be calculated using the following formula.

$$\text{CFOE} = (\text{SpO}_2 - \text{rScO}_2) / \text{SpO}_2, \text{ where}$$

SpO2= peripheral arterial saturation obtained from pulse oximeter

rScO2= Cerebral oxygen saturation obtained from NIRS monitor

Normal range for CFOE = 0.15- 0.33

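### The High BP / High NIRS flash card in Appendix 8 prints the normal blood-pressure range, contradicting its own label and duplicating another card's criteria

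*Protocol*

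**What the plan says.** Appendix 8 of the protocol lists eight flash cards, each headed by a blood-pressure state and a NIRS state with their limits. The card at issue is headed "High BP(MBP =3-90 th Centile) and High NIRS( >85" (per cent). Four other headings bear on it:

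- Normal BP with high NIRS: "Normal BP(MBP =3-90 th Centile) and High NIRS( >85"
- Normal BP with low NIRS: "Normal BP(MBP =3-90 th Centile) and Low NIRS( <55"
- High BP with normal NIRS: "High BP(MBP >90 th Centile) and Normal NIRS( 55 - 85"
- High BP with low NIRS: "High BP(MBP >90 th Centile) and Low NIRS( <55"

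Elsewhere in the readable text, Study Procedure item 3c fixes only the lower limit: "MBP less than the third centile for the gestational age will be taken as low BP for the study". Appendix 2 fixes the NIRS limits: "The normal reference range of rScO 2 for preterm infants varies between 55% and 85" per cent. High blood pressure is defined only on the cards.

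Study Procedure item 10 states what the cards are for: "each pathway in the comprehensive guidelines will be transcribed into individual flash cards that will be easily accessible to study team".

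**The concern.** The same blood-pressure range carries the label Normal on two cards and High on a third, and the third shares its NIRS limit with one of the two. A heading whose label and number disagree does not tell the user which to follow.

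This matters because guideline-based interpretation is part of what separates the multimodal arm from the standard arm, and the cards are the quick-reference form of that guideline. If two members of the study team resolved the contradiction differently, infants in the same state could be assessed along different pathways. The intervention would then be applied less uniformly than the protocol intends. This stake is conditional, because the content of the pathways cannot be seen.

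**Working it through.** No figure in the plan describes card coverage, so the check is a count of headings against states.

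**Inputs.** MBP bands of below the 3rd, 3rd-90th and above the 90th centile (Study Procedure item 3c for the lowest band, Appendix 8 for all three). rScO2 bands of below 55%, 55-85% and above 85% (Appendix 2 and Appendix 8). The eight headings are taken as printed. I treat the 3rd-90th and 55-85% ranges as including their end points.

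**Number of states.** 3 × 3 = 9 cells. One cell (both values normal) is not a deviation and has no card, which looks intended. That leaves 9 − 1 = 8 abnormal states for 8 cards.

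**Cards matching each state by printed limits:**

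| MBP centile | rScO2 <55% | rScO2 55-85% | rScO2 >85% |
|---|---|---|---|
| <3rd | 1 (Low/Low) | 1 (Low/Normal) | 1 (Low/High) |
| 3rd-90th | 1 (Normal/Low) | none (not a deviation) | **2** (Normal/High and High/High) |
| >90th | 1 (High/Low) | 1 (High/Normal) | **none** |

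**Result.** Six abnormal states match exactly one card, one matches two and one matches none. Cards: 6 × 1 + 1 × 2 = 8. Distinct criterion pairs: 6 + 1 = 7. Both faults come from the single High BP / High NIRS heading. Three states have rScO2 above 85%. Low BP with high NIRS is the third, and it is unaffected.

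**Can other text settle it?** Item 3c defines low pressure only. Appendix 2 covers NIRS only. Appendix 5, the parent guideline, is a figure that is not shown. Nothing readable resolves the heading.

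**Trial size.** The sample-size section uses means of 30 and 22.5, SD 15, two-sided alpha 0.05 and power 0.80. The standardised difference is 7.5/15 = 0.5. The t-based calculation gives 63.77, so 64 per arm and 128 in total, as stated. None of these inputs involves the cards.

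**The case against.** The strongest answer is that this is a slip in one heading and that the set largely corrects itself. The card is labelled High BP, its two High BP neighbours print a different limit, and a Normal BP / High NIRS card already exists. A user who follows the label sees no overlap and no gap; both appear only to a user who reads the number and ignores the label. This stands, and it lowers the likely practical effect. It does not make the heading consistent.

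The cards are also aids rather than the whole assessment. Item 3e makes the comprehensive guideline the tool for reaching an assessment, and item 3f has the findings weighed in clinical context. That is fair, although item 10 describes the cards as transcriptions of that guideline, so they should agree with it.

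The link to the result is also remote. The Rationale concerns treatment of low pressure, and all three Low BP cards agree with item 3c. The heading touches only non-low pressure with rScO2 above 85%, and the protocol does not say how often that occurs.

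A reader might go further and infer that infants in the same state were sent down different pathways, or that their safety was affected. The document does not support this. The card bodies and Appendix 5 are not shown, so it is unknown whether the two pathways differ, whether the card's figure prints its own limit, or whether Appendix 5 states the range clearly.

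**Conclusion.** The inconsistency is real and lies wholly within Appendix 8: one of eight headings contradicts its own label and the other two High BP cards, and repeats the criteria of the Normal BP / High NIRS card. By the printed numbers, one abnormal state is covered twice and one not at all. It most likely reflects a heading error, but it is a wrong decision limit on a tool used in the multimodal arm and should not stay as printed.

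Neither the number of infants concerned nor any loss of uniformity can be estimated from the protocol. Alpha, power and N are unaffected. The conclusion assumes that the headings were extracted correctly from the PDF. The other two High BP headings came through with a different and complete limit, so an extraction fault is unlikely. Which limit belongs on the card is a clinical matter on which this review takes no view.

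**What to change.** Reconcile the High BP / High NIRS heading with the other Appendix 8 cards and with the Appendix 5 guideline, so that each of the eight abnormal BP/NIRS states maps to exactly one card, and reissue the card. The cost is one corrected heading and one replaced card.

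If assessments have already been made, list the Appendix 7 reports with rScO2 above 85% and MBP not below the 3rd centile, and count the infants in each of the two affected states. The form records blood pressure in mmHg without a centile or category, so each such report needs a look-up against the chart named in item 3c. The form has no field for the card used. The list can therefore show how many infants were in the affected states, but not which card was followed.
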